**Fig. 2 Fig2:**
[figure not shown]
SEHNeCa exercise programme. M1: Low to moderate intensity; M2: moderate intensity; M3: intensive moderate intensity; 1RM: 1 maximum repetition

**Table 3 Tab3:** Exercise intensity categories

Zone^a^	%HRR^b^	RPE^c^	Training type
High intensity training	> 85	> 5.5	High intensity training. The patient nears exhaustion and is no longer in a steady state
M3	60–84	4.5–5.5	Moderate to intensive training. The patient has difficulties in talking and sweating increases
M2	40–59	3–4	Moderate intensity. The patient notices an increased respiratory rate
M1	20–39	1–2.5	Low to moderate intensity. The patient does not notice any increase in the respiratory rate
Low-intensity training	< 20	< 1	Low intensity. This involves daily activities requiring low levels of effort

^a^The intensity zones are based on the estimated maximum heart rate and applying specific intensity boundaries based on HRR (43,44)

^b^HRR: heart rate reserve. Maximum heart rate—resting heart rate

^c^RPE: rating of perceived exertion. Determined using the Borg scale from 0 to 10 (45)

### Autonomous exercise intervention

Every patient in the control group will receive the corresponding standard treatment (i.e. radiotherapy), determined by the regular oncological consensus committee. In addition, they will receive a prescription concerning healthy lifestyles and a personalised exercise plan, together with an evaluation and individualised nutritional intervention by a physician at the Endocrinology and Nutrition department in Cruces, Basurto or Galdakao Hospitals, in the same way as for intervention groups. They will also be evaluated in the radiation oncology department with the routine follow-up (end of radiotherapy, one, three, six and twelve months after radiotherapy) to assess outcomes and toxicity due to oncological treatment according to Radiation Therapy Oncology Group and Common Terminology Criteria for Adverse Events (vs 5.0) toxicity criteria.

### Statistical analysis

Differences between treatment groups in changes in outcome variables will be estimated on an intention-to-treat basis. We will use linear mixed models for longitudinal analysis of repeated measurements of continuous outcomes (SAS PROC MIXED) and generalised logistic mixed models for dichotomous outcomes (SAS PROC GLIMMIX), considering intercept and time courses as random effects and testing the significance of the interaction of time slopes for each treatment group. No imputation method will be used to handle missing data, as longitudinal mixed-effect models based on maximum likelihood estimation are more appropriate for handling missing data than common imputation methods such as the last observation carried forward, complete case analysis, or other possible forms of imputation [29].

A sample size of 40 patients per group (120 in total) will give 80% power to the study to detect as significant (0.05) the difference at six months in a mean lean body mass loss of 25% between the control and rehabilitation groups, and of 12% between the rehabilitation and prehabilitation groups, corresponding to an estimated mean lean body mass loss from baseline of 4.8 kg (9.1%) in the control group, 3.6 kg (6.8%) in the rehabilitation group, and 3.2 kg (6%) in the prehabilitation group (standard deviation 2,4 kg). With an anticipated drop-out rate of 20%, we plan to enrol 144 patients (48 per group).

During these first 12 months of recruitment, the radiation oncology departments of Basurto and Cruces University Hospitals have attended 161 eligible patients, 112 met the inclusion criteria, of whom 63.4% agreed to participate in the study. Therefore, we expect that the recruitment period will last 24 months.

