**Methods:**

Patients with squamous cell carcinoma of the head and neck (*n* = 144), treated with radiotherapy, will be randomly assigned to one of 3 comparison groups: pre-radiotherapy supervised exercise, post-radiotherapy supervised exercise and autonomous exercise, stratifying by human papillomavirus infection and previous surgery.

The exercise programme will be carried out in 36 sessions over 12 weeks, combining moderate and high intensity strength and aerobic exercises. The main outcome variable is the change in lean body mass at 6 months measured by bioimpedance, while secondary variables are functional capacity, symptoms, quality of life and adverse effects. Longitudinal generalised mixed models will be used for the analyses of the repeated measurements at 3, 6, and 12 months after baseline.

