## Methods/design

### Trial design

The SEHNeCa project is a multicentre, randomised, controlled clinical trial with three arms. Patients are recruited by the radiation oncologist at the patient’s first visit to the radiation oncology department, where they are asked to participate in the programme. Four assessments are made of all the participants, regardless of the group they belong to, at 0, 3, 6 and 12 months.

The baseline assessment will be performed during the same week as recruitment. After randomisation, the pre-radiotherapy group will start the supervised PE programme (at least 7–10 days before starting radiotherapy). The control and post-radiotherapy groups will initially receive physical activity guidelines that they can perform independently. The post-radiotherapy group will start supervised training 4–6 weeks after finishing radiotherapy and the control group will not have supervised training.

All the patients will receive follow-up by the endocrinology service (before radiotherapy, during radiotherapy, at the end of radiotherapy and one month, 3 months, 6 months and 12 months after the end of radiotherapy) in which they will receive screening and assessment of nutritional status as well as individualised nutritional intervention following international guidelines [19], which may include nutritional advice, oral nutritional supplementation, and/or insertion of a feeding tube as required by each patient (Table 1) (Fig. 1).

**Table 1 Tab1:** SEHNeCa Programme timeline

Follow up	D0	W1	W2		W3		W4		M2		M3		M4	M5	M6	M7	M12	M18
**Diagnosis and recruitment**	**X**																	
**Nutritional evaluation**		**X**									**X**				**X**		**X**	**X**
**Radiation oncology evaluation**	**X**										**X**		**X**		**X**		**X**	**X**
**Radiotherapy**					X													
**Measurements**		**X**											**X**			**X**	**X**	
**Supervised Exercise Intervention**			**PRE-RADIOTHERAPY GROUP**															

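### The analysis of continuous outcomes compares changes and time slopes and names no baseline adjustment; adding one is a nearly free gain in precision, probably small for lean body mass and larger for function tests and questionnaires

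*Protocol article*

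**What the plan says.** The abstract (Methods) defines the primary outcome: "The main outcome variable is the change in lean body mass at 6 months measured by bioimpedance". The Trial design section says that baseline is collected in every arm: "Four assessments are made of all the participants, regardless of the group they belong to, at 0, 3, 6 and 12 months".

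The Statistical analysis section sets the scale of the comparison: "Differences between treatment groups in changes in outcome variables will be estimated on an intention-to-treat basis". Linear mixed models are planned for continuous outcomes and logistic mixed models for dichotomous ones, "considering intercept and time courses as random effects and testing the significance of the interaction of time slopes for each treatment group". The section gives the random effects and the term to be tested. It does not list the fixed effects, so it does not say whether a group main effect is fitted. It mentions no baseline covariate and no constraint on the baseline means.

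The documents leave open whether month 0 is part of the response. The Trial design section counts four assessments including month 0, while the abstract speaks of "analyses of the repeated measurements at 3, 6, and 12 months after baseline".

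**The concern.** A random intercept lets patients differ in level. It does not adjust the group comparison for baseline. Three models fit the text:

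- **Response is the change at 3, 6 and 12 months.** The comparison is unadjusted for baseline.
- **Month 0 is in the response and group has a main effect.** The arm means at baseline are free. With complete data, the group-by-time contrast amounts to an unadjusted difference in change.
- **Month 0 is in the response and there is no group main effect.** The arms share a baseline mean, and the comparison is baseline-adjusted.

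The first two are the usual forms, and only the third uses the baseline fully. Under the first two, any relation between the baseline value and later change stays in the error term. What is at stake is precision, in a trial planned with 40 evaluable patients per arm and little power to spare.

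**Working it through.** **Inputs from the Statistical analysis section.** Mean 6-month losses are 4.8 kg (9.1%) in control, 3.6 kg (6.8%) in rehabilitation and 3.2 kg (6%) in prehabilitation. The SD is 2.4 kg, read here as the SD of change because it follows the mean losses. There are 40 patients per arm and alpha is 0.05, taken as two-sided because the text does not say.

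**Assumptions, not in the document.** The between-patient SD of lean body mass, S, is 5–12 kg (8–12 kg in step 3). Baseline-to-follow-up correlations for secondary outcomes are 0.5–0.7. Power is from the noncentral t or F distribution for a single 6-month comparison. The few degrees of freedom spent on adjustment are ignored.

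**1. The plan's own figure.** The mean of the three losses is 3.867 kg, and the squared deviations sum to 0.871 + 0.071 + 0.444 = 1.387. The noncentrality is 40 × 1.387 / 2.4² = 9.63, and the three-group F test has 78.9% power, close to the stated 80%. Control versus rehabilitation alone (1.2 kg, so 1.2/2.4 = 0.5 SD) has 59.8%. These are the unadjusted starting points.

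**2. Lean body mass, equal variances at baseline and 6 months.** The correlation is rho = 1 − 2.4²/(2S²). The ratio of adjusted variance to change-score variance is (1 + rho)/2.

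| S (kg) | rho | Variance ratio | Three-group power | Control vs rehabilitation |
|---|---|---|---|---|
| 5 | 0.885 | 0.942 | 81.4% | 62.4% |
| 6 | 0.920 | 0.960 | 80.6% | 61.6% |
| 8 | 0.955 | 0.978 | 79.9% | 60.8% |
| 10 | 0.971 | 0.986 | 79.5% | 60.4% |
| 12 | 0.980 | 0.990 | 79.3% | 60.2% |

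Adjustment saves 1–6% of variance and adds 0.4–2.5 points to either power figure.

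**3. Lean body mass, if kg loss is proportional to baseline.** This is an added assumption. With the mean rate of the two compared arms, (9.1% + 6.8%)/2 = 7.95%, the correlation of baseline with loss is r = 0.0795 × S/2.4. The adjusted SD is 2.4 × √(1 − r²).

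| S (kg) | r | Variance saved | Control vs rehabilitation |
|---|---|---|---|
| 8 | 0.27 | 7% | 62.9% |
| 10 | 0.33 | 11% | 64.8% |
| 12 | 0.40 | 16% | 67.2% |

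Against 59.8%, the gain is about 3–7 points.

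**4. Function tests and questionnaires.** In units of the cross-sectional variance, change has variance 2(1 − rho) and the adjusted estimate 1 − rho². Power is shown for an illustrative difference of 0.5 cross-sectional SD.

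| rho | Change | Adjusted | Variance saved | Power, change → adjusted |
|---|---|---|---|---|
| 0.5 | 1.00 | 0.75 | 25% | 59.8% → 72.2% |
| 0.6 | 0.80 | 0.64 | 20% | 69.5% → 78.8% |
| 0.7 | 0.60 | 0.51 | 15% | 81.4% → 87.1% |

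**5. What a chance baseline imbalance leaves behind.** The standard error of the baseline difference between two arms is S × √(2/40), or 1.12–2.68 kg for S = 5–12. A change score already subtracts that difference. Under the model of step 2, the remainder per one-standard-error imbalance is (1 − rho) times it: 0.13 kg at S = 5 and 0.05 kg at S = 12. That is 4–11% of the planned 1.2 kg. It is 13–32% of the planned 0.4 kg between rehabilitation and prehabilitation.

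**The case against.** The strongest objection is that the text is silent, not wrong. The fixed effects are not listed, a condensed article may leave covariates to an analysis plan that is not shown, and one model compatible with the wording already adjusts for baseline. This stands in part: a reader might infer that the authors have decided against baseline adjustment, and the document does not say so. But the section does more than omit a detail. It fixes the scale (changes), the random effects and the tested term, and both usual forms of that model are unadjusted. Stating which model is meant would settle the point either way.

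Other stronger readings also fail:

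- **Bias.** A reader might conclude that baseline imbalance biases the result. Randomisation makes the change comparison valid, and change scores remove most of any imbalance. Only the chance remainder in step 5 is left.
- **Every outcome.** The abstract says that "secondary variables are functional capacity, symptoms, quality of life and adverse effects". Adverse effects have no baseline value of this kind.
- **A large gain for the primary outcome.** The percentages in the sample size paragraph re-express mean losses against a common mean of about 53 kg (4.8/0.091 = 52.7; 3.6/0.068 = 52.9; 3.2/0.06 = 53.3). They do not show that heavier patients lose more kg, so step 3 is a possibility, not a finding.

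It is also fair that the calculations compare a single change with its adjusted counterpart. They do not give the exact loss for a slope test over all visits, so they indicate size only.

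**Conclusion.** The point holds as one of efficiency for the continuous outcomes. As written, the analysis is an unadjusted comparison of change unless month 0 is in the response without a group main effect. Such a comparison is valid, but in large samples it is never more precise than the adjusted one.

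For lean body mass the benefit is probably small, as in step 2. The larger pairwise gain in step 3 depends on proportional loss, which the document does not establish. For function tests and questionnaires it may be material, but the correlations behind the 15–25% saving are assumptions. Baseline adjustment would not close the gap between the roughly 60% pairwise power found in step 1 and the 80% stated for "to detect as significant (0.05) the difference at six months"; that is a separate matter.

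**What to change.** In the Statistical analysis section, state that each continuous-outcome model adjusts for the baseline value of that outcome, in one of two ways:

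- model the 3-, 6- and 12-month values, with baseline and baseline-by-visit terms as covariates; or
- keep month 0 in the response and constrain the three arm means to be equal there, with no group main effect. This also keeps patients who have only a baseline value.

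Name the 6-month lean body mass contrast first, then the function tests and questionnaires. Adverse effects are outside this change. If the intended model already has a common baseline mean, saying so is enough.

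The cost is one sentence, a small change to the planned PROC MIXED code and a few degrees of freedom. Baseline is already measured in all arms, so no data, visits or patients are added. Fixing the choice in advance also removes a decision that would otherwise be made with the data in view.

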### Randomisation

Randomisation is carried out on a central basis through the coordinating committee. This will be made up of the organization responsible for the study’s management and the researchers. The committee will be blind to the assignment of patients in the comparison groups and will convene in the Primary Health Research Unit of Bizkaia.

The 120 patients included in the study will be randomly assigned and consequently registered and attached to one of the three study groups in a 1:1:1 ratio, through randomisation by random blocks of 3 or 6 patients. Patients are stratified according to HPV status and previous surgery yes/no.

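### Randomisation is stratified by HPV status and previous surgery, but the mixed model as described leaves both factors out; if they predict the change in lean mass, the test is conservative and its intervals too wide

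*Protocol article*

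**What the plan says.** The Randomisation section allocates patients "to one of the three study groups in a 1:1:1 ratio, through randomisation by random blocks of 3 or 6 patients", and adds: "Patients are stratified according to HPV status and previous surgery yes/no". The Methods part of the abstract agrees ("stratifying by human papillomavirus infection and previous surgery").

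The Statistical analysis section sets the aim: "Differences between treatment groups in changes in outcome variables will be estimated on an intention-to-treat basis". It names the SAS procedures for continuous and dichotomous outcomes and then describes the model as "considering intercept and time courses as random effects and testing the significance of the interaction of time slopes for each treatment group". Neither stratification factor is mentioned, nor is any other covariate. The section does not call the analysis unadjusted or say that the listed terms are the whole model. It also does not say how baseline lean mass is handled.

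**The concern.** Stratified blocks make the arms nearly equal on HPV status and previous surgery. If these factors affect how much lean mass a patient loses, the difference between arms varies less from one randomisation to the next than a model without them assumes. Such a model counts the between-stratum variation as error. Its standard errors are then too large, its intervals too wide and its true type I error below 5%.

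The trial would carry the burden of stratifying without collecting the precision. There is also a link to missing data. The plan relies on likelihood-based models without imputation and expects 20% drop-out. That is valid if missingness is random given what is in the model, and including the two factors makes the assumption easier to defend if they relate to drop-out. The article does not document such a relation.

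**Working it through.** **Inputs from the Statistical analysis section.** Mean losses are "estimated mean lean body mass loss from baseline of 4.8 kg (9.1%) in the control group" and "3.6 kg (6.8%) in the rehabilitation group, and 3.2 kg (6%) in the prehabilitation group (standard deviation 2,4 kg"), with 40 per group and a 0.05 level, taken here as two-sided. The control versus rehabilitation difference is 4.8 − 3.6 = 1.2 kg.

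**Assumed input.** R², the share of variance in lean-mass change explained by the two factors, is not given. The range used is 0 to 20%.

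**1. The plan's own figure.** SE = 2.4 × √(2/40) = 0.537 kg, so 1.2/0.537 = 2.236. Power = Φ(2.236 − 1.960) = Φ(0.276) = 60.9%, not 80%; 80% would need 63 per group. A global three-group F test at 40 per group gives 78.9%, which may be where the 80% comes from. That is a separate matter. Here 60.9% is the starting value at R² = 0.

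**2. Ignoring the strata.** With arms balanced within strata, the true SE is 0.537 × √(1 − R²), but the test still uses 0.537.
- True type I error = 2 × [1 − Φ(1.960/√(1 − R²))]
- Power = Φ((2.236 − 1.960)/√(1 − R²))

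**3. Using the strata.** The test uses the smaller SE.
- Power = Φ(2.236/√(1 − R²) − 1.960)
- 95% interval half-width = 1.960 × 0.537 × √(1 − R²)

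| Assumed R² | √(1 − R²) | True type I error, unadjusted | Power, unadjusted | Power, adjusted | Half-width, unadjusted / adjusted (kg) |
|---|---|---|---|---|---|
| 0% | 1.000 | 5.0% | 60.9% | 60.9% | 1.05 / 1.05 |
| 5% | 0.975 | 4.4% | 61.2% | 63.1% | 1.05 / 1.03 |
| 10% | 0.949 | 3.9% | 61.4% | 65.4% | 1.05 / 1.00 |
| 20% | 0.894 | 2.8% | 62.1% | 70.5% | 1.05 / 0.94 |

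All power figures use the normal approximation, so the columns compare like with like. The gain is about 2, 4 and 8 percentage points.

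**4. Check by simulation.** 120 patients in four strata, blocks of 3 or 6, assumed factor prevalences of 40% and 50%, 4,000 runs per setting, analysing change. At R² of 5, 10 and 20%:
- Type I error was 4.5, 4.5 and 3.0% unadjusted, and 5.0, 5.2 and 4.7% adjusted.
- Power was 59, 61 and 62% unadjusted, and 61, 65 and 70% adjusted.

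The formulas assume perfect balance within strata, which unfinished blocks only approximate. The Monte Carlo error of the type I rates is about 0.3 points.

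**5. Which terms matter in the described model.** Steps 2 and 3 compare change at one time point. For the random-intercept-and-slope model, the generalised least-squares SE of the treatment-by-time term was computed for 120 patients, strata balanced over arms, months 0, 3, 6 and 12. Assumed values were an intercept SD of 7 kg, slope SD of 0.35 kg/month, residual SD of 1.1 kg and a stratum effect on level of 5 kg per factor.

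| Assumed stratum effect on slope (kg/month) | SE, no strata terms | SE, main effects only | SE, main effects and strata-by-time | Full / none |
|---|---|---|---|---|
| 0 | 0.0830 | 0.0830 | 0.0830 | 1.00 |
| 0.1 | 0.0845 | 0.0845 | 0.0830 | 0.98 |
| 0.2 | 0.0888 | 0.0888 | 0.0830 | 0.93 |
| 0.3 | 0.0956 | 0.0956 | 0.0830 | 0.87 |

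The random intercept absorbs a stratum difference in level, so main effects alone do nothing for the tested term. Only strata-by-time terms help, and only if the strata affect the rate of change. Intercept–slope correlations of −0.3 and 0.3 give the same SEs.

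**The case against.** The strongest reply is that silence is not a statement. This is a condensed journal article. The sentence on the model names the random effects and the tested term, and a covariate list is commonly left to the analysis plan, which is not shown. Stratified randomisation and a covariate list kept elsewhere are compatible. This stands in part. A reader might infer that the model holds only time and treatment terms, and the article does not say so. What remains is that a description specific enough to name the procedures, the random effects and the test does not carry the design's strata. Anyone following it as written would not adjust.

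A second reply is that the harm is conditional. This stands in full. A reader might infer that power is certainly being lost, but no R² is given and at R² = 0 nothing is lost. At 5% the gain is about two points of power.

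Third, the omission does not bias the estimate or inflate the type I error; the test errs on the conservative side. That is also right, and it limits how serious the point can be.

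Fourth, low power for 1.2 kg is a sample-size matter and should not lend weight here. Agreed. Nor would adjustment cure it: reaching 80% at 40 per group would need an R² of about 0.36 (1 − 40/62.8).

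**Conclusion.** The point holds in a limited form. The design uses HPV status and previous surgery, and the model as described does not. If the factors explain 5 to 20% of the variance in lean-mass change, following that description gives a true type I error of about 4.4 to 2.8% and forgoes about 2 to 8 points of power for the 1.2 kg difference. The interval half-width would be 1.05 kg where 1.03 to 0.94 kg was available.

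These sizes rest on the assumed R², near-complete balance within strata, the plan's SD of 2.4 kg and a two-sided test. The documents do not support a claim that the trial's analysis is unadjusted, that precision is certainly lost, or that results would be biased. If the full analysis plan already includes the factors with their time interactions, confirming that closes the point. It is worth doing because it is nearly free, not because the trial's validity depends on it.

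**What to change.** State in the Statistical analysis section, before any comparison by arm, that HPV status and previous surgery enter the primary and secondary mixed models as fixed effects, each with its interaction with time. The interactions should be named explicitly, since main effects alone leave the precision of the treatment-by-time term unchanged. State also how baseline lean mass is handled: either a baseline mean constrained to be equal across arms or baseline as a covariate.

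Both factors must be known at randomisation, so no new data are needed. The cost is a sentence or two in the plan and a few degrees of freedom. If the factors prove unrelated to lean-mass change, almost nothing is lost.

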## Introduction

Head and neck cancer (HNC) was the seventh most frequently diagnosed cancer worldwide in 2020 [1]. The main risk factors that cause this type of cancer to develop are smoking, alcoholism, diet, sedentary lifestyle, obesity and human papillomavirus (HPV) infection, among others [2]. This unhealthy background added to both the disease and its treatments effects tremendously reduce cardiorespiratory capacity, lean body mass (through accelerated processes of cachexia and sarcopenia) bone mass, and provoke psychosocial distress, depression, pain, fatigue, and impaired cognitive function [3].

Between 30 and 50% of HNC patients have malnutrition and it has been estimated that they may experience 5–10% weight loss during radiotherapy treatment [4, 5]. Weight loss of more than 5% has been associated with a decrease in overall and specific survival for head and neck cancer. In addition, it is estimated that more than 70% of weight loss can be attributed to loss of lean body mass, which leads to a decrease in strength, functional capacity and quality of life [6]. Because of that lean body mass is considered an appropriate and feasible end point in clinical trials of HNC. Additionally, sarcopenia before and after treatment is an independent factor of poor prognosis associated with decreased survival in patients undergoing radiotherapy with curative intent [7]. Moreover, sarcopenia has recently been associated with increased acute toxicity (grade ≥ 3 dysphagia) [8] and decreased progression-free survival [9]. For this reason, it is deemed appropriate to perform body composition measurements as part of the diagnosis and evaluation of interventions for HNC [10–12].

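### A random intercept and time slope does not assure the standard error of the 6-month difference in lean body mass; an unstructured covariance over the four visits would

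*Protocol article*

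**What the plan says.** The Statistical analysis section of the protocol article plans SAS PROC MIXED for continuous outcomes, "considering intercept and time courses as random effects" and "testing the significance of the interaction of time slopes for each treatment group". It names no other covariance structure. It does not say whether time is a number or a category, or how a 6-month difference is to be taken from the fitted model.

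The target is a single time point. The Abstract states: "The main outcome variable is the change in lean body mass at 6 months measured by bioimpedance". The sample size paragraph is likewise set "to detect as significant (0.05) the difference at six months", with an SD of 2.4 kg. Under Trial design, assessments are made "at 0, 3, 6 and 12 months".

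On the shape of the loss, the Introduction says of patients with head and neck cancer that "they may experience 5–10% weight loss during radiotherapy treatment", and attributes more than 70% of weight loss to lean mass.

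**The concern.** A random intercept with a random straight-line slope makes each patient's departure from the group mean a line plus independent noise. Suppose instead that patients differ in how much they lose during radiotherapy and that the loss then stays. Each departure is then a step between baseline and month 3, followed by a plateau. The later changes from baseline correlate strongly with one another, while baseline stands apart. The fitted model has to average the large early step with the small later fluctuations, so the variance it implies for the change from baseline to month 6 need not be the true one.

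At stake are the width of the confidence interval and the p-value for the primary outcome. The direction of the error depends on which test is taken from the model, and the article leaves that partly open: it words a slope test but aims at a 6-month difference.

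**Working it through.** **Inputs from the article.** Visits at 0, 3, 6 and 12 months; 40 patients per group; SD 2.4 kg, taken as the SD of the 6-month change; alpha 0.05, taken as two-sided; planned 6-month losses of 4.8, 3.6 and 3.2 kg.

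**Inputs assumed.** The correlation r between a patient's changes at different visits; SD 2.4 kg at all three later visits; baseline SD 9 kg, unrelated to the later change (6 and 12 kg give the same rates for r = 0.5–0.8); complete data.

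**The plan's own figure.** The article says that 40 per group "will give 80% power to the study". The true standard error of a 6-month difference is 2.4 × √(2/40) = 0.537 kg. For 1.2 kg (control versus rehabilitation), power is Φ(1.2/0.537 − 1.96) = Φ(0.28) = 61%. For 0.4 kg it is 11%, and for 1.6 kg 85%. So 80% is not reproduced for the two contrasts that the article names. That is a separate matter; what this point uses is the 0.537 kg.

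**Reading A: visits as categories, 6-month contrast, stated random effects kept.** For each true 4 × 4 covariance S, the limiting fitted covariance V minimises log|V| + tr(V⁻¹S) over all random-intercept-plus-slope forms. With c = month 6 minus baseline, the variance ratio is c′Vc / c′Sc, and the false-positive rate is 2 × [1 − Φ(1.96 × √ratio)].

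| True correlation of changes | Variance ratio | False-positive rate |
|---|---|---|
| r = 0.3–0.4 | above 1 | 3–4% |
| r = 0.5 | 0.999 | 5.0% |
| r = 0.6 | 0.894 | 6.4% |
| r = 0.7 | 0.787 | 8.2% |
| r = 0.8 | 0.681 | 10.6% |
| serial, 0.8/0.6/0.8 | 0.734 | 9.3% |
| SD growing 1.5/2.4/4.3 kg | above 1 | about 4% |

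Worked line for r = 0.7: 1.96 × √0.787 = 1.739, and 2 × [1 − Φ(1.739)] = 8.2%. The reported standard error would be 0.537 × √0.787 = 0.476 kg.

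The value 0.5 is neutral for a simple reason. With a random intercept and independent noise of variance σ², each change has variance 2σ² and two changes share σ², so r = σ²/2σ² = 0.5. The stated model contains that case exactly.

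**Wider assumptions for reading A.** These vary the shape of the patient-level loss, its share of the heterogeneity and the residual SD (0.3–1.4 kg), with baseline SD 8 kg:
- Loss by month 3 that holds or partly recovers: about 5.5–18%.
- Loss spread to month 6, then flat: up to 22%.
- Recovery to 0.7 and 0.3 of the loss at months 6 and 12: 5–8%.
- Recovery to 0.6 and 0.1: 3–5%.
- Straight-line patient trajectories: 5.0%.

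**Reading B: time linear in the mean, slope-by-group test as worded.** The rate was 5% or less in every scenario. With a common mean loss of 4.8 kg by month 3 that persists, and equal SDs, the standard error is about 1.4–1.5 times too large. At a ratio of 1.475, the rate is 2 × [1 − Φ(1.96 × 1.475)] = 2 × [1 − Φ(2.891)] = 0.4%. Over the equal-SD covariances it is about 0.4–0.7%.

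**Simulation, 40 per arm.** One set used about 1,400 trials per setting. Reading A gave 7.0% against 4.6% unstructured at r = 0.7, and 12.3% against 6.1% at r = 0.8. The 12.3% lies about two simulation standard errors above 10.6%, since √(0.106 × 0.894/1400) = 0.8 points. A second set of 385–600 trials per scenario gave:

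| Scenario (residual SD) | Reading A | Reading B | Unstructured, 6-month contrast |
|---|---|---|---|
| Plateau (1.0 kg) | 9.5% | 4.7% | 4.3% |
| Plateau (1.4 kg) | 7.3% | 5.5% | 4.7% |
| Partial recovery (1.0 kg) | 11.4% | 0.5% | 5.5% |

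**The case against.** The strongest objection is that reading A is not what the article describes. The only test it words is the interaction of time slopes, and for that test p-values are nominal or too large. This stands. A reader might infer that the plan's standard error is too small and its false-positive rate 6–11%; the article does not support that, because the inflation needs categorical visits and a 6-month contrast, and neither is stated for the model.

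Second, the covariance is assumed. The Introduction gives an average weight loss, not how patients vary around it, and an early mean loss does not by itself make a covariance wrong. Nor is persistence documented: one arm starts supervised training 4–6 weeks after radiotherapy, and strong recovery by month 12 reverses the error. This also stands, and is why the size can only be given as a range.

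Third, this is a condensed article. Residual structure, robust standard errors and the coding of time are commonly left to a SAP, time courses need not mean straight lines, and a random-coefficient model is a standard choice. This stands in part. Silence on those details is no fault. But the article does name a random structure and a slope test, and sets both beside an endpoint at one visit. Under early, persistent loss with equal SDs, the slope test gives too large a standard error. The 6-month contrast gives too small a one if the changes correlate above about 0.5.

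**Conclusion.** The point holds in a conditional form. The stated random effects do not assure the standard error for the 6-month comparison.

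- **6-month contrast with categorical visits.** The standard error is too small when changes correlate above about 0.5 and too large below that. With equal SDs, the false-positive rate is about 6–11% for r = 0.6–0.8 and 3–4% for r = 0.3–0.4. Over wider assumptions it is about 3–22%.
- **Linear slope-by-group test as worded.** The rate is 5% or less. It falls below 1% under a persistent early mean loss with equal SDs, and the cost is power.

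Early and persistent loss is plausible from the Introduction but is not documented as a covariance, so neither the sign nor the size can be fixed from the article. The case for changing the plan is that four fixed visits need no such restriction, and that the unstructured covariance stayed near 5% in the settings simulated (4.3–6.1%).

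**What to change.** For continuous outcomes, replace the random intercept and time course by:
- visit as a class variable with visit-by-group means;
- an unstructured covariance over the four scheduled visits (PROC MIXED, REPEATED / TYPE=UN) with Kenward-Roger degrees of freedom;
- the group contrast in change from baseline to month 6, named as the primary test in place of the slope interaction.

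State a fallback in advance: if the model does not converge, use a simpler structure with empirical (sandwich) standard errors.

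The cost is a line or two of analysis text. Covariance parameters rise from 4 (two variances, one covariance, one residual) to 10 (4 × 5/2), which 120–144 patients support. Intervals will be somewhat wider wherever the stated model would have been over-optimistic.
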